## 12 STATISTICAL CONSIDERATIONS

### 12.1 SAMPLE SIZE

In our previous COG-Reduc trial (NCT01788618) conducted among 168 patients randomized in 3 groups (56 patients per group), we have observed a difference of 5.2 points (16.3, Standard Deviation SD 14.7 vs 11.1, SD 14.8) on the FACT-Cog PCI in favour of the software-based cognitive stimulation program supervised by a neuropsychologist as compared to a home-based unsupervised cognitive stimulation exercises using a dedicated booklet (Dos Santos et al., 2020).

Given that the present proposal aims to assess the added value of remotely supervision by a neuropsychologist of an online cognitive stimulation, as compared to an online cognitive stimulation without any supervision, we similarly expect a mean difference of score change between end of program (at 12 weeks) and baseline of at least 5.2 points in the continuous FACT-Cog PCI between experimental and control arms.

As suggested previously (Bell et al., 2018), such difference is clinically important. Using a two sample t-test with equal variances (allocation-ratio 1:1, bilateral alpha risk 0.05, power 80%) and assuming a standard deviation of 14.7, 127 assessable patients per arm are required. To anticipate 15% of non-assessable patients, we plan to enrol 300 patients (150/arm).

### 12.2 STATISTICAL ANALYSIS

All analyses will be described in a detailed statistical analyses plan (SAP), and will be performed using the intent-to-treat (ITT) population. Any deviation to SAP and protocol changes that may occur after study initiation will appear and discussed in the final report of the study.

#### 12.2.1 Primary objective

The continuous FACT-Cog PCI subscale difference between the end of the 12-week intervention and baseline measures will be computed and compared between experimental and control groups by using a bilateral Student test.

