## 6 ENDPOINTS

### 6.1 PRIMARY ENDPOINT

The primary endpoint is the average change in the score of the Perceived Cognitive Impairment (PCI) subscale score of the Functional Assessment of Cancer Therapy–Cognitive Function (FACT-Cog) after completion of the 12-weeks program (T1), as compared to the baseline score.

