#### ❖ Inclusion and randomization procedure

Patients who meet all the eligibility criteria will be included in the study.

Before randomization takes place, patients will undergo, at the investigating center, an evaluation of various parameters required for stratification of the randomisation.

Randomisation will be stratified on:

- **Age:** <55 versus ≥55-year old,
- **Composite criterion** based on **fatigue, anxiety, and depression level:** score <37 at the FACIT-F self-report questionnaire for evaluation of fatigue, and/or score >11 at the HADS scale for evaluation of depression/anxiety versus no abnormal score at any of these questionnaires.
- **Physical activity level** (low, moderate, high, as assessed using a VAS)

Patients will then be randomized in a 1:1 ratio to be assigned to either:

- **Experimental arm:** 12-weeks of remotely supervised online cognitive stimulation program
- **Active control arm:** 12-weeks of open access to online cognitive exercises without any supervision.

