#### 12.2.2 Secondary objectives

Self-reported outcomes (quality of life questionnaires) and objective cognitive evaluations will be measured by scores and described as follows:

- Quantitative variables will be summarized using quartiles and range (mean and standard deviation for Gaussian-like variables).
- Categorical variables will be summarized using numbers and proportions.

To measure evolution through time, comparison of scores between two assessments will first be performed by paired T-test (or the Wilcoxon signed-rank test for paired data for non-gaussian variables) in each group. Then, comparison of cognitive evolution between groups will employ a linear mixed model with random patient effect, adjusted on age, composite criteria of fatigue/anxiety/depression, current physical activity (stratification criteria).

For all statistical analysis, two-sided p-values <0.05 will be considered statistically significant.

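### The primary t-test on PCI change fixes the baseline slope at 1 and omits the stratification factors, giving up precision that data already being collected could supply

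*Protocol*

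**What the plan says.** Section 6.1 defines the primary endpoint as the average PCI change "after completion of the 12-weeks program (T1), as compared to the baseline score". Section 12.2.1 states that this difference is "computed and compared between experimental and control groups by using a bilateral Student test" and names no covariate.

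Section 12.1 sizes the trial on the same unadjusted test. It expects a "mean difference of score change between end of program (at 12 weeks) and baseline of at least 5.2 points", with "allocation-ratio 1:1, bilateral alpha risk 0.05, power 80" per cent, and concludes: "assuming a standard deviation of 14.7, 127 assessable patients per arm are required". The source figures from the sponsor's previous trial are given as "16.3, Standard Deviation SD 14.7 vs 11.1, SD 14.8", without saying whether they describe change scores or scores at one time point.

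Section 7.4.2 introduces three factors with "Randomisation will be stratified on": age (two levels), the fatigue/anxiety/depression composite (two levels) and physical activity (three levels). Section 12.2.2 compares cognitive evolution between groups with a linear mixed model "adjusted on age, composite criteria of fatigue/anxiety/depression, current physical activity (stratification criteria"). Neither analysis lists baseline PCI as a covariate.

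**The concern.** The sponsor treats the three factors as prognostic enough to stratify on and to adjust for in a secondary model, but leaves them out of the test that decides the trial. That test also handles baseline PCI in one fixed way: subtracting it is the same as setting its regression slope to 1. When the baseline/T1 correlation is below 1 and the two variances are equal, the best-fitting slope is smaller. The change score then loses precision and over-corrects for any chance difference between arms at baseline.

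There is also an overlap. Sections 5.2 and 6.2 list PCI at T1 again among the secondary objectives and endpoints. The same T1 contrast can therefore come out of the unadjusted primary test and of the adjusted mixed model, both read at p<0.05, and the two may differ. At stake are the precision of the primary estimate and a clear rule on which T1 result counts.

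**Working it through.** **Inputs.** From Section 12.1: difference 5.2, SD 14.7, two-sided alpha 0.05, power 80%, 127 assessable per arm, 15% non-assessable. Assumptions: 14.7 is the SD of change; baseline and T1 variances are equal; the baseline/T1 correlation rho runs from 0.3 to 0.9; the strata explain a share R² of 2%, 5% or 10% of the variance of change. The protocol gives neither rho nor R².

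**1. Reproduce the plan.** A two-sample t-test (noncentral t) with 5.2 and 14.7 needs 126.4, so 127 per arm, and has 80.2% power at 127. Then 127/0.85 = 149.4, so 150 per arm and 300 in total. The stated figures hold.

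**2. Add baseline PCI.** With a common variance σ², the change score has variance 2σ²(1 − rho) and the ANCOVA residual has variance σ²(1 − rho²). The ratio is (1 + rho)/2, so the ANCOVA SD is 14.7 × √((1 + rho)/2).

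| rho | variance ratio | ANCOVA SD | power at 127/arm | t-test n/arm for the same precision |
|---|---|---|---|---|
| 0.3 | 0.65 | 11.85 | 93.6% | 127/0.65 ≈ 195 |
| 0.5 | 0.75 | 12.73 | 90.0% | 127/0.75 ≈ 169 |
| 0.7 | 0.85 | 13.55 | 86.1% | 127/0.85 ≈ 149 |
| 0.8 | 0.90 | 13.95 | 84.1% | 127/0.90 ≈ 141 |
| 0.9 | 0.95 | 14.33 | about 82% | 127/0.95 ≈ 134 |

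**3. Add the strata only.** With SD 14.7 × √(1 − R²), power is 81.0%, 82.2% and 84.1% for R² of 2%, 5% and 10%. That is a gain of about 1 to 4 points over 80.2%. Baseline PCI and strata together, at rho 0.5 and R² 5%, give about 91.4%.

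**4. Type I error when the strata are ignored.** Stratified allocation balances the strata, but the t-test still counts their variance as noise. The actual alpha is about 2 × P(Z > 1.96/√(1 − R²)), which gives 4.8%, 4.4% and 3.9% for R² of 2%, 5% and 10%. A simulation with 12 strata (2 × 2 × 3), 254 patients and 6,000 runs gave 4.7%, 4.7% and 3.6%. The test is mildly conservative.

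**5. Chance imbalance.** The change score over-corrects by (1 − rho) for each point of baseline difference. The implied single-time SD is 14.7/√(2(1 − rho)) = 12.4, 14.7 or 19.0 at rho 0.3, 0.5 or 0.7. The standard error of the baseline difference is that SD × √(2/127) = 1.56, 1.84 or 2.38 points. A baseline difference of one standard error leaves an error of 1.09, 0.92 or 0.71 points, against a target of 5.2.

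**6. If 14.7 is instead a single-time SD.** The t-test on change would have 66%, 80% or 95% power at rho 0.3, 0.5 or 0.7, and ANCOVA 84%, 90% or 98%. ANCOVA is ahead under this reading too.

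**The case against.** The best defence is that the plan is coherent. Endpoint, sample size and test all concern the same unadjusted change, the arithmetic reproduces, and omitting the strata does not inflate type I error. This stands. A reader might infer that the trial ignores baseline PCI, leaves imbalance uncorrected, or is invalid or under-sized. The protocol does not support any of these: baseline is subtracted, imbalance in it is over-corrected, stratified randomisation limits imbalance on the other three factors, and on its stated inputs the test has its planned power.

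The size of the gain is also open to challenge. It rests on an unstated rho and shrinks to 2 to 4 points at rho 0.8 to 0.9. Differencing removes stable stratum effects on the level of PCI, so an R² of 10% for change may be generous. This also stands, and the gains are therefore shown as a range.

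An adjusted secondary model beside an unadjusted primary test is ordinary, and Section 12.2.1 names one primary test. The overlap is therefore minor and needs only a sentence. Section 12.2 defers detail to an SAP that is not shown. It may hold an adjusted sensitivity analysis, but the protocol itself already fixes the primary test.

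The most substantive objection concerns the covariate. The full FACT-Cog is completed up to three weeks after randomisation (Section 7.5.3) in an open-label trial (Section 7.1), so knowledge of the arm could affect the baseline score. This does not favour the t-test where the shift is confined to the baseline report: the change score then carries it in full, and ANCOVA carries it only multiplied by the fitted slope. A shift that persisted to T1 would behave differently. Neither analysis removes the problem, which has to be solved by the timing of the assessment.

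**Conclusion.** The point holds as a loss of efficiency and consistency in a valid, correctly sized analysis. Under equal variances, the primary test gives up precision at any rho below 1. With 14.7 as the SD of change, ANCOVA at 127 per arm would raise power from 80% to between 82% (rho 0.9) and 94% (rho 0.3). Nearly all of this comes from baseline PCI. The case for including the strata rests mainly on consistency with the design and the secondary model, on a gain of about 1 to 4 points, and on removing a mild conservatism (alpha 3.9% to 4.8% under the R² values assumed). The direction is firm; the size cannot be fixed from the protocol. The change is worth making because it needs no extra patients or data, but the trial does not fail without it.

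**What to change.** Before any outcome data are seen, rewrite Section 12.2.1 along these lines: the change in PCI from baseline to T1 will be analysed by ANCOVA with arm, baseline PCI, age group, composite criterion and physical-activity level as randomised; the adjusted mean difference between arms with its 95% CI is the primary estimate. Modelling change gives the same arm effect as modelling T1 PCI once baseline is a covariate, and it keeps the endpoint wording in the synopsis and Section 6.1.

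Keep the Student test as a supportive analysis. State in Section 12.2.2 that the T1 PCI contrast from the mixed model is not a second test of the primary hypothesis.

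Separately, have the FACT-Cog PCI completed before randomisation, for example with the stratification questionnaires.

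The analysis change costs a paragraph in the protocol and SAP, with no new data and no change to the 300 patients. If it counts as a substantial modification under Section 14.1, it also needs coordinator, sponsor and ethics committee approval, and information to the competent authority. Moving the PCI changes the visit schedule for patients not yet randomised.

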#### 12.2.2 Secondary objectives

Self-reported outcomes (quality of life questionnaires) and objective cognitive evaluations will be measured by scores and described as follows:

- Quantitative variables will be summarized using quartiles and range (mean and standard deviation for Gaussian-like variables).
- Categorical variables will be summarized using numbers and proportions.

To measure evolution through time, comparison of scores between two assessments will first be performed by paired T-test (or the Wilcoxon signed-rank test for paired data for non-gaussian variables) in each group. Then, comparison of cognitive evolution between groups will employ a linear mixed model with random patient effect, adjusted on age, composite criteria of fatigue/anxiety/depression, current physical activity (stratification criteria).

For all statistical analysis, two-sided p-values <0.05 will be considered statistically significant.

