#### **Assessments after the intervention**

Evaluations will be performed **on-site**:

- at the end of the intervention (T1 = 3 months),
- 3 months (T2= 6 months) after the end of the intervention, and
- 9 months (T3= 12 months) after the end of the intervention

Each evaluation will include as follows:

- Cognitive complaints: FACT-Cog self-report questionnaire
- Quality-of-life: FACT-G, EQ-5D-5L
- Sleep quality: ISI self-report questionnaire
- Fatigue: FACIT-F self-report questionnaire
- Anxiety/depression: HADS self-report scale
- Physical activity level: IPAQ self-report questionnaire
- Return to work
- Laboratory Assessments:
  - Hematology (CBC, platelets, Hemoglobin)
  - Serum biochemistry (Sodium, potassium, chloride, calcium, creatinine, glucose, ferritin)
  - Thyroid-function testing: thyroid-stimulating hormone [TSH].
- Delivery of patient diary at T0, T1 and T2
- An optional biological sample collection will be proposed at the end of the intervention

Additionally, participants will complete the CNS Vital Signs neuropsychological testing battery to evaluate objective cognitive functions. This will be a self-administered test on their personal computer **at home**, with instructions provided by a clinical research assistant via an information booklet prior to the test.

|                              |                                                                                                                                                                                                                                                                                                                                                                                    |
|------------------------------|------------------------------------------------------------------------------------------------------------------------------------------------------------------------------------------------------------------------------------------------------------------------------------------------------------------------------------------------------------------------------------|

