### 6.2 SECONDARY ENDPOINTS

In both groups, the secondary endpoints are the following:

- Adherence rate to the program (proportion of patients who realized at least 24 out of 36 sessions planned for the entire program)
- At each time evaluation (baseline (T0), end of the program (T1), 3 months (T2) and 9 months (T3) after the end of the program), the following parameters will be assessed:
  - Self-report cognitive complaint scores, including the PCI subscale and three other subscales of the FACT-Cog (perceived cognitive abilities, impact on quality of life, and comments from others).

- Scores of objective cognitive domains (attention, memory, executive functions and processing speed) assessed with the software CNS Vital Signs (CNS VS),
- Quality of life scores (FACT-G + EQ-5D-5L),
- Fatigue scores, evaluated with the self-report questionnaire Functional Assessment of Chronic Illness Therapy-Fatigue (FACIT-F),
- Sleep scores, evaluated with the self-report questionnaire Insomnia Severity Index (ISI),
- Anxiety and depression, evaluated with the self-report questionnaire Hospital Anxiety and Depression Scale (HADS),
- The level of physical activity will be evaluated using the International Physical Activity Questionnaire (IPAQ)
- The proportion of patients who return to work, the delay from randomization to date of return to work, and conditions of return to work (full or part-time, teleworking, professional retraining etc...),
- Measure of the biological parameters
- The Cost of the intervention and the incremental cost-effectiveness ratio in € per Quality-Adjusted Life Year (QALY)

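### Read as written, the secondary mixed model imposes one between-visit correlation on visits at 0, 3, 6 and 12 months; if correlation falls with time, the T3 test rejects too often

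*Protocol*

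**What the plan says.** Protocol section 12.2.2 gives the between-group method for the secondary outcomes: "comparison of cognitive evolution between groups will employ a linear mixed model with random patient effect". The only covariates listed are the three factors used to stratify randomisation. The sentence names no other random effect, no residual covariance structure and no coding of time.

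Section 6.2 lists the occasions: "At each time evaluation (baseline (T0), end of the program (T1), 3 months (T2) and 9 months (T3) after the end of the program"). The synopsis (section 1, assessments after the intervention) puts these on a common time scale, with T1 labelled as month 3, T2 as month 6 and the last visit given as "9 months (T3= 12 months) after the end of the intervention". Counted from the start of the programme, the visits therefore fall at 0, 3, 6 and 12 months.

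The primary outcome is handled differently. Under section 12.2.1 the T1 minus T0 change in PCI is "compared between experimental and control groups by using a bilateral Student test". Section 12.2 adds: "All analyses will be described in a detailed statistical analyses plan (SAP"). That plan is not available here.

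**The concern.** A random patient intercept with independent residuals is compound symmetry. It assumes that T0 and T1, three months apart, correlate exactly as strongly as T0 and T3, twelve months apart. Repeated questionnaire and cognitive scores often correlate less as the interval widens. The model cannot represent that, so it attaches one averaged variance to the T1, T2 and T3 changes alike.

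What is at stake is the claim that the benefit of supervision lasts. Section 4.2 gives this as the purpose of the two later follow-up visits, section 5.2 makes change at T1, T2 and T3 a secondary objective, and section 12.2.2 calls any two-sided p-value below 0.05 significant. If the T3 standard error is too small, that comparison is declared significant too often when there is no effect.

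**Working it through.** **The plan's own figure.** The protocol gives no number for the mixed model. Its sample size (section 12.1) does reproduce. With a difference of 5.2, SD 14.7, two-sided 5% and 80% power, the normal approximation gives 2 × (1.960 + 0.842)² × 14.7² / 5.2² = 125.4, so 126 per arm. The exact t calculation gives 127 (power 80.2%), as stated. Then 127 / 0.85 = 149.4, so 150 per arm. I use n = 127 per arm below.

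**Inputs.** Visit times come from the protocol. The between-visit correlations are my assumptions, since the protocol gives none. I also assume equal variances, complete data, visits treated as categories and contrasts against T0.

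**Formulas**, with variances scaled to 1:

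- True variance of the change from T0 to Tk: 2 × (1 − ρ₀ₖ).
- Variance the random-intercept model uses for every change: 2 × (1 − ρ̄), where ρ̄ is the mean of the six pairwise correlations.
- Ratio of model to true standard error: r = √[(1 − ρ̄) / (1 − ρ₀ₖ)].
- True size at nominal 5%: 2 × [1 − Φ(1.96 r)].

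**Worked case: exponential decay, 3-month correlation 0.75.** The correlations are 0.75 (two pairs), 0.5625 (two pairs), 0.4219 and 0.3164, so ρ̄ = 0.5605.

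- T1: r = √(0.4395 / 0.25) = 1.33, size 0.9%.
- T2: r = √(0.4395 / 0.4375) = 1.00, size 5.0%.
- T3: r = √(0.4395 / 0.6836) = 0.80, size 11.6%.

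**Effect on T1 power in the same case**, for a 0.25 SD effect. The true SE is √(0.5 × 2/127) = 0.0887 and the model SE is √(0.8789 × 2/127) = 0.1176. With the correct variance, power is Φ(0.25/0.0887 − 1.96) = 80%. With the random intercept it is Φ[(0.25 − 1.96 × 0.1176)/0.0887] = 59%. This concerns T1 comparisons made with the mixed model, not the primary test.

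**Range over assumed structures:**

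| Correlation pattern | T1 size | T2 size | T3 size |
|---|---|---|---|
| Exponential, 3-month correlation 0.5 to 0.9 | 1.9% to 0.6% | 5.5% to 4.5% | 8.6% to 13.6% |
| Linear, falling 0.01 to 0.02 per month from 0.6 or 0.7 | 4.1% to 3.0% | 4.9% to 4.7% | 6.5% to 8.5% |
| Equal correlations | 5.0% | 5.0% | 5.0% |
| Baseline less correlated with follow-up (below) | 6.5% | 8.0% | 9.5% |

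The last row takes T0 with T1/T2/T3 at 0.55/0.50/0.45, T1–T2 at 0.75, T2–T3 at 0.70 and T1–T3 at 0.65, which is a valid correlation matrix. Here ρ̄ = 3.60/6 = 0.60. At T1, r = √(0.40/0.45) = 0.94; at T2, r = √(0.40/0.50) = 0.89; at T3, r = √(0.40/0.55) = 0.85.

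**Why T3 is the firmer half.** The T0–T3 interval contains every other interval. If correlation falls as the interval widens and variances are equal, ρ₀₃ is the smallest of the six. The true T3 variance is then above the average that the model uses. T1 has no such guarantee unless correlation depends on the gap alone.

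**The equal-variance assumption matters.** With a common correlation of 0.6 and a baseline variance of 0.6 against 1 at follow-up, r = 1.05 at every follow-up visit (size 4.0%), which is slightly conservative.

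**Checks.** Fitting the model to simulated data (3-month correlation 0.7, 127 per arm, 150 runs) gave one mean model SE of 0.126 at all three visits, against empirical SDs of 0.097, 0.127 and 0.151. The ratios are 1.30, 1.00 and 0.84; the formula gives 1.30, 1.00 and 0.82. Coding time as linear instead does not help: the slope test's size is 10 to 16% under the exponential patterns and 7 to 9% under the linear ones.

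**The case against.** The strongest reply is that the protocol sentence is incomplete rather than wrong. It does not say that the patient effect is the sole covariance term. It excludes neither a random slope nor a structured residual covariance, and section 12.2 defers detail to a SAP. This stands in part: the SAP could specify an unstructured covariance without contradicting the protocol. But the sentence names a method and lists its covariates, and a statistician following it would ordinarily fit a random intercept. It is fair to propose a better-specified method at that place.

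The second reply is that the correlations are assumed. This stands, and it limits what can be claimed. A reader might infer that the T1 standard errors are certainly too large and the T3 ones certainly too small. The documents do not support that. Equal correlations give no error at any visit. The T1 direction also reverses when baseline tracks follow-up less closely than follow-ups track each other, which is plausible here because the intervention lies between T0 and T1. A reader might also take roughly 11% at T3 and 1% at T1 as the expected sizes; those belong to steep decay, and gentler decay gives much smaller departures.

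The third reply is that the primary result is untouched. This stands in full: the Student test on T1 change and the sample size built on it do not use this model.

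**Conclusion.** The point holds conditionally. If the random patient effect is the only covariance term, the secondary between-group model uses one correlation for unequally spaced visits and one averaged standard error for every change from baseline. With equal variances and correlation falling over time, the T3 comparison is anti-conservative: about 6.5 to 8.5% under slow linear decay and 8.6 to 13.6% under exponential decay, against a nominal 5%. T1 size is then usually below nominal (about 0.6 to 4%), with loss of power, but it can exceed nominal, as in the 6.5% example. The damage is confined to secondary analyses, mainly the T2 and T3 comparisons behind a claim of lasting benefit. Severity is minor to moderate.

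**What to change.** In section 12.2.2, replace the random-patient-effect phrase with a mixed model for repeated measures: visit as a category, arm-by-visit interaction, unstructured within-patient covariance, Kenward-Roger degrees of freedom and the existing stratification covariates. Name a simpler covariance structure with robust standard errors as the fallback if the model does not converge. The SAP should carry the same specification.

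The unstructured form does not depend on which correlation pattern is true, so the unknown correlations need not be guessed. The cost is one sentence and no new data. The downside is a few more covariance parameters: 4 variances + 6 covariances = 10 for four visits, which 300 patients support easily.

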### 5.2 SECONDARY OBJECTIVES

The secondary objectives are to assess and compare the two groups of breast cancer patients based on various parameters:

- Individual adherence of patients to the online cognitive stimulation program in each group
- Change in cognitive complaints at T1 (end of intervention), T2 (3 months after the intervention) and T3 (9 months after the intervention)
- Change of objective cognitive performances at T1, T2 and T3
- Health-related quality of life of patients at T1, T2 and T3
- Physical activity levels at T1, T2 and T3
- Changes of fatigue, sleep, anxiety and depression of patients at T1, T2 and T3
- The relationship between fatigue, sleep, anxiety, depression, physical activity and cognitive complaints/performances
- The proportion of patients who return to work at T1, T2 and T3 among working patients
- The change in biological parameters
- The medico-economic impact of the intervention (See the “Medico-economic study” section)

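### One p<0.05 rule covers every secondary test and the within-arm paired tests, so chance findings are likely and within-arm significance cannot show what supervision adds

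*Protocol*

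**What the plan says.** Section 12.2.2 closes with a single rule for the whole trial: "For all statistical analysis, two-sided p-values <0.05 will be considered statistically significant". The protocol gives no order of testing, no adjustment and no exploratory label for secondary results.

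The same section sets out two steps for change over time. In each group separately, "comparison of scores between two assessments will first be performed by paired T-test" (or by Wilcoxon signed-rank). A linear mixed model, adjusted for the stratification factors, then compares the arms. That model is named only for cognitive change.

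Sections 5.2 and 6.2 list an unranked set of outcomes to be compared between the groups at T1, T2 and T3: four FACT-Cog subscales, four CNS Vital Signs domains, quality of life, fatigue, sleep, anxiety and depression, physical activity, return to work and laboratory values, with adherence as well.

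The primary analysis is separate and clean. Sections 6.1 and 12.2.1 give one endpoint (PCI change), one time point (T1) and one two-sample test. Section 12.2 defers analysis detail to a SAP, which was not available here.

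**The concern.** There are two problems, and both come from the stated rule rather than from anything left unsaid.

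First, every secondary contrast gets the same 0.05 threshold as the primary. Section 4.2 expects secondary results to carry weight: it looks to objective cognition for a benefit of supervision, and to the follow-up visits for continued benefit. If the primary is negative, some secondary score may well cross 0.05 by chance, and the protocol would allow it to be called statistically significant.

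Second, the rule covers paired tests inside each arm. Sections 7.4.3 and 8 give both arms the same 12-week program on the same platform; the arms differ by supervision. A within-arm change mixes the effect of the exercises, natural recovery and retest effects with any effect of supervision, so its p-value does not address the trial's question. For the non-cognitive scores (fatigue, sleep, anxiety and depression, physical activity, quality of life), a literal reading of section 12.2.2 leaves the paired tests as the only inferential tests named, although section 5.2 promises a comparison of the groups.

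**Working it through.** **1. The plan's own figure.** Section 12.1 expects a difference of "at least 5.2 points in the continuous FACT-Cog PCI between experimental and control arms" at two-sided 0.05 and 80% power, and concludes: "assuming a standard deviation of 14.7, 127 assessable patients per arm are required".
- Normal approximation: n = 2(1.960 + 0.842)² × (14.7/5.2)² ≈ 125.5, so 126 per arm.
- Two-sample t: 126.4, so 127 per arm.
- With 15% non-assessable: 127/0.85 = 149.4, so 150 per arm and 300 in all.

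The figure reproduces. It uses the full 0.05 for one primary test, and nothing below changes it.

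**2. Number of secondary contrasts.** The protocol gives no count. From section 6.2, taking one total score for FACT-G and one value each for EQ-5D-5L and IPAQ:
- FACT-Cog 4 + CNS Vital Signs 4 + FACT-G 1 + EQ-5D-5L 1 + FACIT-F 1 + ISI 1 + HADS 2 + IPAQ 1 = 15 scores.
- One contrast per visit, less the primary: 15 × 3 − 1 = 44.
- Literal reading, mixed model for cognitive scores only: 4 + 4 = 8 scores, so 8 tests (one per score) or 8 × 3 − 1 = 23 (one per visit).
- Paired tests against baseline: 15 × 3 × 2 arms = 90.

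**3. Error rates if supervision has no effect on any outcome.** Expected false positives = 0.05m, whatever the correlation. Under independence, the probability of at least one is 1 − 0.95^m.

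| Between-arm tests | m | Expected false positives | P(at least one), independent |
|---|---|---|---|
| Cognitive scores, one test each | 8 | 0.40 | 0.34 |
| Cognitive scores by visit | 23 | 1.15 | 0.69 |
| All scores, one test each | 15 | 0.75 | 0.54 |
| All scores by visit | 44 | 2.2 | 0.90 |

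These scales are correlated, so independence overstates the last column. A multivariate normal simulation of 15 scores at three visits (45 contrasts), with assumed correlations of 0.2 to 0.7 between scores and 0.5 to 0.7 between visits, gave 0.49 to 0.83. The working range for the score-by-visit contrasts is therefore about 0.5 to 0.9.

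**4. Within-arm tests.** For the previous trial, section 12.1 reports: "we have observed a difference of 5.2 points (16.3, Standard Deviation SD 14.7 vs 11.1, SD 14.8) on the FACT-Cog PCI". I read the arm values as changes, in line with section 4.2, which bases its expected difference in change on that trial. With n = 127:
- Unsupervised booklet arm: t = 11.1 / (14.8/√127) = 11.1/1.313 = 8.5.
- Supervised arm: t = 16.3 / (14.7/√127) = 16.3/1.304 = 12.5.
- Smallest significant mean change: about 1.98 × 14.7/√127 = 2.6 points (also 2.6 with SD 14.8).

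On these figures both arms would be significant whether or not supervision adds anything.

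**The case against.** Four points can fairly be made against this.

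**The SAP may deal with it.** Ordering and adjustment of secondary tests are commonly left to the SAP, and their absence from a protocol is no finding. That stands for any missing hierarchy. It does not rescue the sentence itself, which fixes 0.05 for all analyses. A SAP that labelled secondary results exploratory would have to be reconciled with it.

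**A reader might infer that false positives are near certain.** Adding 36 laboratory contrasts (12 values at three visits), adherence (1) and return to work (4) to the 44 gives 85 tests and a 98.7% chance of at least one false positive. The documents do not support that as a headline. Section 12.2.2 names no between-arm test for laboratory values, one test per visit is an assumption, and 98.7% needs independence as well as every null being true.

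**A reader might also infer that the paired tests will often favour supervision falsely.** If both arms shared a true change of 2 to 3 points (SD 14.7, n = 127), one-arm power would be 0.33 to 0.63. Exactly one arm would then be significant 44% to 50% of the time. The misleading pattern is the supervised arm alone, which is p(1 − p), or 22% to 25%. The assumed change has no source in the protocol and lies where this probability peaks. At 5 points it is about 3%; at 11.1 it is practically nil. For PCI the likelier outcome is that both arms are significant, which is uninformative.

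**The plan does not call within-arm change efficacy.** Section 12.2.2 uses the paired tests to describe change over time, and for cognitive outcomes the between-arm model follows. That stands: how the p-values would be reported is a prediction. What remains is that the protocol declares them significant although they do not bear on supervision.

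**Conclusion.** The point holds as a problem of interpreting secondary results. Under the stated rule, false positives among them are likely: about 2.2 expected over 44 score-by-visit contrasts, with a familywise error of about 0.5 to 0.9. On the narrowest reading, cognitive scores only, it is 0.34 to 0.69. These figures assume no effect of supervision on any outcome, my count of scores, independence for the narrow reading and the upper end of the wider range, and the correlations stated above for the lower end.

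The within-arm tests cannot isolate supervision, because the exercise program is common to both arms. The t of 8.5 assumes that the previous trial's booklet arm is a guide to the control arm here and that its 11.1 is a change score.

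The primary conclusion and the 300 patients are not affected. This is an inexpensive improvement to what the trial may claim, not a flaw in its main test.

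**What to change.** Replace the closing sentence of section 12.2.2 with text to this effect: the two-sided 0.05 level applies to the primary endpoint; secondary between-arm contrasts are reported as estimates with 95% confidence intervals and are exploratory. Replace the within-arm paired tests with the mean change in each arm and its 95% confidence interval, presented as description. If the SAP already says this, bring the protocol sentence into line with it.

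Optionally, name a short family of key secondary endpoints in advance, to be tested only if the primary is significant. Which endpoints belong there, and by what procedure, is the sponsor's choice.

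The cost is wording only: no change to data collection, sample size or the primary analysis. The downside is that fewer secondary results can be called statistically significant.
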